### 6.2 Secondary endpoints

The time points below are the *corrected age* of the infant, calculated from expected date of full-term birth (not the chronological age calculated from actual date of premature birth). For some secondary outcomes only a subsample of infants will be studied.

Respiratory function: Need for surfactant, number of days in ventilator, number of days in CPAP, number of days requiring oxygen.

Heart rate variability: Postpartum, after 48-72 hours, at discharge and at 3-4 months.

Thermal regulation: Axillary temperature is measured continuously, alternatively every hour on infant, and if in SSC also on parent.

Infections: Proportion of infants that experience sepsis during admission in the neonatal ward according to case record, and total number of days treated with antibiotics.

Breastfeeding, nutrition, and growth: Age at first feed, age at first passage of meconium, time to full enteral feeding, time to weaning from feeding tube, lowest weight, time to return to birth weight, weight gain in grams per day during admission, and weight at discharge as well as term age as per case record. Nutrition and breastfeeding status will be completed weekly according to the Index of Breastfeeding Status (IBS) questionnaire during hospital stay, at discharge, at term age, at 3-4 months of age and at 12 months. The Breastfeeding Self-Efficacy Questionnaire (BSES) will be completed at 7 days, 3-4 months, and the Infant Breastfeeding Assessment Tool (IBFAT) each week during admission, at discharge, at term age and at 3-4 months.

Epigenetics: Whole genome analysis as well as locus specific methylation of stress related genes for Oxytocin receptor (OXTR), glucocorticoid receptor (NR3C1), Arginine-vasopressin receptor (AVP), Proopiomelanocortin (POMC), Glutamate decarboxylase-1 (GAD1), Glutamate receptor (GRM1), Brain-Derived Neurotrophic Factor- (BDNF), serotonin transporter (SLC6A4 och SERT), serotonin receptor (5H2A) och serotonin degradation enzyme (MAOA) in cord blood postpartum, in buccal swabs postpartum and at 6 hours, whole blood from opportune time during first 6 hours, whole blood and buccal swabs at 48-72 hours, at 3-4 months and at 24 months of age.

Microbiota: Infant colonization by microbiome (bacteria) is identified by DNA analysis from fecal samples at 0-6 hours, 72 hours, 3-4 months, 12 och 24 months, and compared to the parents. Vaginal, rectal, and skin samples from mother and partner are collected at 0-6 hours.

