### **8.6 Determination of allocation**

Randomization will be done by electronic means, close to the actual birth time but at earliest 6 hours before birth and latest one hour after birth.

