# 9 ASSESSMENT OF SAFETY AND EFFECTIVENESS

## 9.1 Assessment of clinical effectiveness

SCRIP-score: Respiratory rate, heart rate and oxygen saturation are measured and scored in a table, need for respiratory support is part of the table. The average of total scores is analyzed.

HRV: Heart rate variability is measured for an appropriate interval, possibly using the "Faros 360" and analyzed according to Porges method by the Nurture Science Programme, Columbia University, NY. Average and median values are analyzed.

Respiration: Need for surfactant, number of days in ventilator, number of days in CPAP, number of days requiring supplemental oxygen collected from hospital case record. Proportions and median values will be analyzed.

Temperature: Axillary temperatures will be recorded. Average and median values are analyzed.

Infection: Proportion of infants experiencing sepsis during admission collected from hospital case record, as well as days receiving antibiotics. Average and median values are analyzed.

Breastfeeding and nutrition: Age at first feed, age at first passage of meconium, time to full enteral nutrition, lowest weight, time to removal of feeding tube, time to regained birth weight, weight gain in grams per day during hospital stay, weight at discharge and at term age is collected from the hospital case record. Breastfeeding status is determined from Index of Breastfeeding Status, Breastfeeding Self-Efficacy Questionnaire and Infant Breastfeeding Assessment Tool (IBFAT). A PhD student will be responsible for extracting data from case record (Take Care and Clinisoft). A research nurse will distribute questionnaires and parents will complete them during admission or at home prior to follow-up visits. Proportions are analyzed.

Epigenetics: Whole genome analysis as well as locus specific methylation of stress related genes for Oxytocin receptor (OXTR), glucocorticoid receptor (NR3C1), Arginine-vasopressin receptor (AVP), Proopiomelanocortin (POMC), Glutamate decarboxylase-1 (GAD1), Glutamate receptor (GRM1), Brain-Derived Neurotrophic Factor- (BDNF), serotonin transporter (SLC6A4 och SERT), serotonin receptor (5H2A) och serotonin degradation enzyme

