### **11.2 Statistiscal analysis**

Primary outcome analysis will be done according to intention to treat (ITT) on all subjects that met inclusion criteria without exclusion criteria and were randomized. Per protocol analysis will also be undertaken based on actual adherence to allocated place of care. For safety measures the entire sample will be included. All continuous variables will be described with sample size and number of observations, average and median values, with standard deviations and minimum and maximum values. All categorical variables will be summarized in frequency tables. For the primary outcome a mixed model-regression analysis will be done to evaluate the effect of gestational age, birth order, single or multiple birth, intrauterine growth retardation, mode of birth (vaginal or caesarean), antenatal corticosteroids given or not, and birth weight. The null hypothesis is that there is no difference in the groups for the primary outcome. The analysis will be done for the whole study population as well as those that received the intervention.

An interim analysis will be done for the primary outcome on the first 30 patients enrolled.

Secondary outcomes that are continuous or categorical will be analyzed by linear or mixed model regression models, and dichotomous variables by logistic regression models. Stratification factors utilized in the randomization will be used as covariates. Qualitative and exploratory methods will be used as required.

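### Birth weight is not in the adjustment set that section 11.2 states for the raw-weight secondary outcomes, so precision is given away that costs nothing to keep

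*Protocol*

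**What the plan says.** Section 11.2 of the protocol contains two covariate rules.

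- **Primary outcome.** A mixed model is fitted "to evaluate the effect of gestational age, birth order, single or multiple birth, intrauterine growth retardation", and the list ends with "antenatal corticosteroids given or not, and birth weight". Gestational age and birth weight are both in it.
- **Secondary outcomes.** "Secondary outcomes that are continuous or categorical will be analyzed by linear or mixed model regression models", with logistic models for dichotomous outcomes. The covariate rule is "Stratification factors utilized in the randomization will be used as covariates". Nothing else is named.

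The stratification factors are not listed anywhere in the protocol. Section 8.6 says "Randomization will be done by electronic means, close to the actual birth time" and mentions no strata, and neither do sections 7.1 and 7.2.

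The growth endpoints in section 6.2 include "lowest weight, time to return to birth weight, weight gain in grams per day during admission", plus weight at discharge and at term age. Section 9.1 repeats them: "time to regained birth weight, weight gain in grams per day during hospital stay, weight at discharge and at term age". Time to regain birth weight cannot be derived without birth weight, so birth weight is collected for every infant who contributes to that endpoint.

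**The concern.** For lowest weight, weight at discharge and weight at term age, birth weight is the baseline value of the quantity being compared. Section 4.3 describes the population as weighing roughly 1 to 2 kg, so infants differ far more in starting weight than place of care could plausibly move them. If birth weight is not in the model, that known spread stays in the residual error.

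The protocol gives birth weight to the SCRIP model, where its link with the outcome is indirect. Its stated rule does not give it to the weight models, where the link is closest. At stake is whether an effect of skin-to-skin contact on early weight loss, in either direction, could be seen with 75 infants per arm or would be reported as no difference.

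**Working it through.** The plan states no SD, correlation or precision for any weight outcome, so there is no figure of its own to reproduce. The check has four steps.

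**1. Could birth weight be a stratum?** Section 7.1 places randomization antenatally, and section 7.2 puts it at the latest one hour before birth. Birth weight does not exist at that point. Section 8.6 differs and allows randomization up to one hour after birth, so the possibility is remote rather than nil.

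**2. Is birth weight a valid covariate?** Yes. It is fixed at birth, before place of care can act on it, and section 11.2 already uses it for the primary outcome.

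**3. Size for lowest weight.** The only input from the protocol is 75 per arm (section 7.1). The rest are assumptions: mean birth weight μ = 1500 g (mid-range of 1–2 kg), birth-weight SD s_B = 250–350 g, mean loss 8%, SD of percentage loss s_L = 3–5 points, loss independent of birth weight.

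With lowest weight = birth weight × (1 − loss):

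- Unadjusted variance = 0.92²·s_B² + μ²·s_L² + s_B²·s_L²
- Variance after adjusting for birth weight = s_L²·(μ² + s_B²)
- 95% CI half-width = 1.96 × SD × √(2/75) = 0.320 × SD
- Power for difference d ≈ Φ(d / (SD × 0.1633) − 1.96)

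At the low end (250 g, 3 points): unadjusted variance = 52,900 + 2,025 + 56 = 54,981, SD 234 g; adjusted SD = 0.03 × √2,312,500 = 46 g.

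At the high end (350 g, 5 points): unadjusted variance = 103,684 + 5,625 + 306 = 109,615, SD 331 g; adjusted SD = 0.05 × √2,372,500 = 77 g.

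| | Not adjusted for birth weight | Adjusted |
|---|---|---|
| SD of lowest weight | 234–331 g | 46–77 g |
| 95% CI half-width | 75–106 g | 15–25 g |
| Power for 45 g (3% of 1500 g) | 22% to 13% | 94.7% or more |

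The correlation with birth weight implied by these inputs is 0.95–0.99. The chance difference in mean birth weight between arms has a standard error of 250 × 0.1633 = 41 g to 350 × 0.1633 = 57 g. That is about as large as the 45 g effect, and it passes almost unchanged (× 0.92) into the unadjusted comparison.

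Would strata based on gestational age remove the problem? Assume two bands split at 31 weeks, gestational age spread evenly, a slope of 150–200 g per week, and an SD of 200 g at a given age. The variance of gestational age within bands is 3²/12 = 0.75 and 2²/12 = 0.333 weeks², weighted 0.6 and 0.4, which gives 0.583. Birth-weight SD within bands is then √(200² + 150² × 0.583) = 230 g to √(200² + 200² × 0.583) = 252 g. Most of the spread remains.

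**4. Size for other outcomes.** Let R² be the share of outcome variance that gestational age and birth weight explain beyond the strata. The protocol gives no value. The SE is multiplied by √(1 − R²), and the difference detectable with 80% power is 2.80 × √(1 − R²) × √(2/75) SD.

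| Assumed R² | SE reduction | Detectable difference |
|---|---|---|
| 0 | 0% | 0.457 SD |
| 0.1 | 5% | 0.434 SD |
| 0.3 | 16% | 0.383 SD |
| 0.5 | 29% | 0.323 SD |

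These figures are for a linear model. Section 9.1 summarises respiratory days by proportions and medians, so for those skewed counts they are only a guide.

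**The case against.** The strongest reply is that section 11.2 says stratification factors will be covariates but does not say that nothing else will be, and a fuller list may sit in an analysis plan that is not shown. That is fair as far as it goes: exclusivity is an inference. But the protocol did choose to state a covariate rule for secondary outcomes, and that rule differs from the one it states a few lines earlier for the primary outcome. Any addition would have to go beyond the text.

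A second reply is that the large gain for lowest weight is partly built in, because lowest weight was modelled as birth weight less a percentage. That also stands in part. The structure is realistic for a nadir soon after birth, but the SDs and the 45 g effect are assumptions, and the result does not carry over to weight at discharge or at term age.

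A third is that section 9.1 speaks of analysing proportions for breastfeeding and nutrition. That does not displace the regression that section 11.2 prescribes for continuous secondary outcomes.

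Four stronger readings are tempting, and the protocol does not support them:

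- **That gestational age is omitted.** It is known before birth and may well be a stratum, in which case it is already a covariate. With the strata unnamed, this cannot be decided.
- **That growth, feeding and respiratory outcomes all lose most of their precision.** For feeding and respiratory days the gain is modest and depends wholly on the assumed R².
- **That birth weight is the baseline for grams per day.** A rate of gain is a different variable and already nets out starting weight. Time to regain birth weight is likewise already referenced to it.
- **That the comparison is biased.** Under randomization the estimate without birth weight is unbiased, and its interval already allows for chance imbalance.

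Finally, section 11.3 claims no power for these outcomes, and section 9.3 describes much of the evaluation as exploratory. That limits the consequence, but it is no reason to leave the precision unused.

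**Conclusion.** The point holds for birth weight and the three raw-weight outcomes. The adjustment set stated in section 11.2 does not include it. It is very unlikely to enter as a stratum, and it is a collected, valid covariate that the protocol already uses elsewhere.

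For lowest weight the loss is large under the stated assumptions: a CI half-width of about 75–106 g where 15–25 g is attainable with the same infants. For weight at discharge and at term age the loss is probably smaller and cannot be fixed from the protocol. For feeding and respiratory-day outcomes the most that can be said is an SE reduction of about 5–29% for R² between 0.1 and 0.5, and less if gestational age is already a stratum.

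This is an inexpensive improvement to unpowered secondary analyses. It does not touch the primary analysis and does not make any stated figure wrong.

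**What to change.** Replace the covariate sentence for secondary outcomes in section 11.2 with:

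> Stratification factors used in the randomization will be covariates. Models for infant growth, feeding and respiratory outcomes will also include gestational age at birth if it is not already a stratum. Models for lowest weight, weight at discharge and weight at term age will also include birth weight.

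Fix this before data are analysed, and list the stratification factors in section 8.6 so that the sentence can be applied as written. Do not extend gestational age to the parental outcomes (questionnaires, maternal imaging, maternal cortisol), for which this argument gives no reason.

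The cost is a change of wording and one or two model degrees of freedom. No new data are needed and nothing in the care of the infants changes. Fixing the covariates in advance also closes off a choice made after seeing results, which is worth having in an unblinded trial (section 8.7) that plans a separate publication for each outcome (section 17).

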### **11.3 Determination of sample size**

Sample size calculations are based on the two studies on immediate SSC in low-birth-weight infants (6,7) where the proportion of maximum SCRIP score at 6 hours of age required 100 infants to reach 90% power with a 2 sided test,  $p=0,05$ . We expect a healthier cohort in Sweden and Norway, so we anticipate a smaller difference between the groups, and therefore plan to include 150 infants for the primary outcome of physiological stabilization. For one of the secondary outcomes, long term psychomotor development, a clinically significant difference of 0,3 SD on the Bayley test, with 80% power and a 2-sided test,  $p=0,05$ , the sample size is 104 patients, very similar to the primary

outcome. For many of the secondary outcomes there are no earlier studies to guide sample size calculation, therefore data will be collected on all possible subjects, or a subsample of what is possible in the circumstances.

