# 1 Summary

## **PROTOCOL IDENTITY AND AIM**

Protocol title: IPISTOSS

Aim of study: To determine if skin-to-skin contact results in a better physiological stabilization, altered epigenetic profile and better long-term neurodevelopmental outcome.

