## 7 METHODS

### 7.1 Method overview

This is a prospective multicenter randomized controlled trial. Screening for study subjects takes place among women with threatening premature birth in the antenatal and labor ward, with randomization taking place antenatally. The study population is 150 infants (75 infants in control and in intervention) born between gestational age 28+0 and 32+6 weeks at Karolinska University Hospital labour wards in Danderyd and Huddinge in Stockholm and at Stavanger Universityhospital in Norway. The intervention is skin-to-skin contact with either parent or with a surrogate chosen by them, the SSC should be uninterrupted during the first six hours of life, and as much as possible in the first 72 hours. Data will be collected during this time, and then during the period of admission, and continued until the infant reaches 24 months corrected age (described further below). Certain selected outcomes will be studied in subsamples of the 150 subjects, and for practical reasons some at only one site. Some families studied may later be transferred elsewhere in the country, data for these will continue to be collected as far as possible. There may also be certain exclusions due to language and interpreter problems that may influence data. Discussion on sample sizes for subsamples is ongoing.

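### The Bayley sample size is wrong: 0.3 SD at 80% power needs about 350 children, not 104, and the planned 150 give at most about 45% power

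*Protocol*

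**What the plan says.** Protocol section 11.3 (Determination of sample size) gives one power calculation for a secondary outcome, long-term psychomotor development. The target is "a clinically significant difference of 0,3 SD on the Bayley test, with 80% power and a 2-sided test", at p=0.05. The conclusion is that "the sample size is 104 patients, very similar to the primary" outcome. The primary-outcome figure in the same paragraph is a total: the earlier studies "required 100 infants to reach 90% power with a 2 sided test", which the sponsor raises to 150.

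Section 7.1 fixes the design as two equal arms: "The study population is 150 infants (75 infants in control and in intervention"). Section 11.2 sets the analysis: "Secondary outcomes that are continuous or categorical will be analyzed by linear or mixed model regression models", with the randomisation stratification factors as covariates. Section 6.2 places the Bayley assessment at 24 months corrected age. No loss to follow-up and no variance reduction enter the Bayley calculation.

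The Summary (section 1) lists "better long-term neurodevelopmental outcome" among the three things the study sets out to determine, beside physiological stabilization and the epigenetic profile.

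**The concern.** A difference of 0.3 SD is small, and a two-arm trial with about 50 children per arm cannot detect it with 80% power. Because the effect is given in SD units, the calculation needs no outside figure and can be checked directly.

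The Bayley is the only secondary outcome with a power statement, and it carries one of the three aims. By calling 104 similar to the primary requirement, in a trial that enrols 150, the text leads a reader to think the Bayley comparison is adequately sized. If it is not, a real difference of the size the protocol itself calls clinically significant would more likely than not be missed. A non-significant result read beside a claim of 80% power for 0.3 SD could then be taken as ruling out an important effect when it does not.

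**Working it through.** **Inputs.** From section 11.3: difference d = 0.3 SD (so SD = 1), power 80%, two-sided alpha 0.05, stated size 104. From section 7.1: two arms of 75, 150 in total.

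**Trying to reproduce 104.** The normal-approximation formula for comparing two means is

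n per arm = 2 × (z for alpha + z for power)² / d²

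= 2 × (1.960 + 0.842)² / 0.3² = 174.4, rounded up to **175 per arm, 350 in total**.

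The t-test version gives 175.4, so 176 per arm and 352 in total. The stated 104 is too small by a factor of 350 / 104 = 3.4.

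**Other readings of 104.**

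| Reading | Result |
|---|---|
| 104 per arm (208 in total) | power 58% (t-test), and more children than the trial enrols |
| One-sided 5% test | 138 per arm, 276 in total; the text says two-sided |
| Unequal allocation | 393 in total at 2:1, 468 at 3:1; the design is 1:1 |
| One-sample formula | (1.960 + 0.842)² / 0.3² = 87.2, so 88; wrong for two arms |
| One-sample 88 with an assumed 15% loss | 88 / 0.85 = 103.5, so 104; wrong formula, and no loss rate is stated |
| Two-arm 350 with an assumed 15% loss | 350 / 0.85 = 411.8, so 412; moves further from 104 |
| Covariate adjustment with 52 per arm | needs correlation √(1 − 52/174.4) = 0.84 between covariates and Bayley score; not claimed |
| d = 0.55 instead of 0.3 | 2 × (1.960 + 0.842)² / 0.55² = 51.9, so 52 per arm, **104 in total** |

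The only reading that gives 104 with the correct two-arm formula and the stated power and alpha is a difference of 0.55 SD.

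**What the trial can detect** (two-sample t-test, two-sided 0.05). The loss rates are assumptions, since the protocol states none.

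| Children assessed | Power for 0.3 SD | Difference detectable with 80% power |
|---|---|---|
| 104 (stated size) | 33% | 0.55 SD |
| 150 (no loss) | 45% | 0.46 SD |
| 135 (10% loss) | 41% | 0.49 SD |
| 128 (15% loss) | 39% | 0.50 SD |
| 120 (20% loss) | 37% | 0.52 SD |
| 105 (30% loss) | 33% | 0.55 SD |

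The normal approximation gives 33.4% for 104 and 45.1% for 150, so the choice of formula does not matter.

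**The case against.** Five points can be made for the plan.

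- **33% is not the trial's own power.** It belongs to 104 children, while 150 are planned. This stands: the figure to quote for the trial is at most about 45%. That is still far below 80%.
- **The effect size, not the number, may be the slip.** This also stands: 104 fits 0.55 SD, and the protocol cannot settle the matter. But the sentence is false as written either way, and if 0.55 SD was meant, the claim to detect the clinically significant 0.3 SD falls away.
- **Covariate adjustment could raise the precision.** For 150 children to reach 80% power at 0.3 SD, covariates would have to explain 1 − 75/174.4 = 57% of the Bayley variance. Section 11.2 names only the stratification factors as covariates for secondary outcomes, and section 11.3 assumes no gain. This does not stand.
- **The Bayley is secondary, and the 150 were chosen for the primary outcome.** True: the correction changes no patient number or endpoint. It does not make the stated power correct, and the outcome carries a headline aim.
- **No decision rule is attached to a null Bayley result,** and section 9.3 describes many outcomes as exploratory. Fair: misreading such a result is a risk, not something the protocol commits to.

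Twins are eligible, since section 8.2 excludes only triplets and higher multiples. How co-twins are allocated is not stated, so neither the direction nor the size of any effect on power can be derived, and none is claimed here.

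**Conclusion.** The concern holds. On the protocol's own inputs the Bayley comparison needs about 350 children, not 104. The stated 80% power is really about 33% at 104, about 45% if all 150 are assessed, and 33% to 41% if between 30% and 10% are lost by 24 months (assumed rates). The 150 have 80% power for about 0.46 SD.

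This rests on a two-arm, 1:1 comparison of means with no covariate gain, as the protocol describes, and treats the infants as independent. The sizing of the primary outcome is not touched. The sentence must be corrected because it misstates the power for one of the three aims by a wide margin.

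**What to change.** Rewrite the Bayley sentence in section 11.3:

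- Establish whether 0.3 SD or 104 was the intended figure, and make effect size, power and number agree.
- State that 0.3 SD with 80% power, two-sided 0.05, would need about 350 children.
- State that the planned 150 have 80% power for about 0.46 SD and about 45% power for 0.3 SD, and give the same figures under a stated loss assumption (for example, about 0.50 SD and 39% if 15% are lost).
- Delete the comparison with the primary outcome's sample size.
- Add, here or in the statistical analysis plan, that the Bayley result will be given as a difference with its 95% confidence interval, and that a non-significant result will not be read as showing no effect.

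The cost is one paragraph and a less favourable figure. No additional patients, visits or changes to the design are needed.
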